## Abstract

**Background:**

After a diagnosis of diabetes mellitus, people not only have to cope with the physical aspects and common complications that require daily self-management, they are also faced with ongoing psychosocial challenges. Subsequently they find themselves having to navigate the health system to engage multidisciplinary supports; the combination of these factors often resulting in reduced health-related quality of life. To maintain optimal diabetes control, interventions need to incorporate psychosocial supports and a skill base for disease management. Therefore, our aim was to evaluate an ‘Optimal Health Program’ that adopts a person-centred approach and engages collaborative therapy to educate and support the psychosocial health of people diagnosed with type I or II diabetes.

**Methods:**

This prospective randomised controlled trial will include 166 people diagnosed with diabetes: 83 in the intervention (Optimal Health Program) and 83 in the control (usual care) group. Participants with type diabetes mellitus will be recruited through hospital outpatient clinics and diabetes community organisations. Participants in the intervention group will receive nine (8 + 1 booster session) sequential sessions, based on a structured treatment manual emphasising educational and psychosocial support self-efficacy and skills building. The primary outcome measures will be generalised self-efficacy (GSE) and health-related quality of life (AQoL-6D and EQ-5D). Secondary measures will be anxiety and depression (HADS), social and workplace functioning (WSAS), diabetes-related quality of life (DQoL), diabetes-related distress (PAID), and type of coping strategies (Brief COPE). In addition, a health economic cost analysis and process evaluations will be performed to assess the economic cost and efficacy of the program’s operations, implementation and service delivery.

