### Participants

A total of 166 participants with a diagnosis of DM will be recruited into the RCT. Inclusion criteria are: (1) have a DM diagnosis, confirmed by medical records; (2) be aged 18 years or above; and (3) be able to converse in English without an interpreter. Exclusion criteria are: (1) presence of developmental disability or amnestic syndrome impairing their ability to learn from the intervention; and (2) comorbid serious acute medical illness defined by the treating physician. As the OHP adopts a holistic approach to managing chronic disease, patients may enter the program at any stage along the continuum of care. De-identified records will be collected on how many people with diabetes were approached or self-referred to the study including reasons for decline, to assess for potential selection bias.

Power was calculated to detect a medium effect size of d = 0.50. This was chosen as a clinically meaningful effect size that may be compared with previous RCT research in the area of chronic disease management programs [28]. The calculations assumed two primary outcomes (health-related quality of life and General Self-efficacy Scale (GSE) scores), four assessment points (baseline, 3-month, 6-month, and 12-month follow-ups), a study-wide type I error rate (α) of .05, and hence a type II error rate (β) of 0.20 (power of 0.80), a correlation of post-treatment scores with baseline measurements (ρ) of 0.81, and a two-tailed statistical test [29]. To detect the effect size of d = 0.50, 66 participants in each of the control and intervention groups will be required. Allowing for up to 20 % attrition, a total of 166 participants, or 83 in each group will be recruited.

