### Outcome measurements

Table 1 displays primary and secondary outcome measures and time points. Primary measures are changes in: health-related quality of life as assessed by the AQoL-6D [26], consisting of six separately scored dimensions of good health and a simple global ‘utility’ score and EQ-5D [27]; and self-efficacy as measured by the General Self-Efficacy Scale (GSE) [34], a general sense of perceived self-efficacy in regarding daily hassles as well as adaptation to stressful life events. Secondary measures are: the Diabetes Quality of Life (DQoL) [35] measure, a screen for problem or risky substance use in adults as assessed by the Alcohol, Smoking and Substance Involvement Screening Test (ASSIST) [36] developed by the World Health Organization (WHO); coping strategies as measured by an abbreviated version of the COPE inventory [37], the Brief COPE [38]; treatment expectancy and rationale credibility in clinical studies as assessed by the Credibility/Expectancy Questionnaire (CEQ) [39]; clinical indices such as body mass index (BMI) and glycated haemoglobin (HbA1c); diabetes-related psychosocial self-efficacy measured by the Diabetes Empowerment Scale (DES) [40]; symptom severity and caseness (number meeting clinical disorder threshold) of anxiety and depression as assessed by the Hospital Anxiety and Depression Scale (HADS) [41]; health care utilisation for economic evaluation purposes assessed by the Health Care Utilisation Questionnaire (HCUQ) [32]; diabetes-related emotional distress measured by the Problem Areas in Diabetes Scale (PAID) [42]; perceived acceptability of treatment assessed using the Treatment Evaluation Inventory-Short Form (TEI-SF) [43]; a 10-item measure of the Big Five Inventory (BFI) personality dimensions [44]; and impact of a person’s mental health difficulties on their ability to function via the Work and Social Adjustment Scale (WSAS) [45].

**Table 1 Tab1:** Primary and secondary outcome assessments and time points for MINDS

Assessment tools	Baseline	3-month	6-month	12-month
Primary outcomes				
AQoL-6D (20 items)	X	X	X	X
GSE (10 items)	X	X	X	X
Secondary outcomes				
DQoL (15 items)	X	X	X	X
ASSIST (6 items)	X	X	X	X
Brief COPE (28 items)	X	X	X	X
CEQ (6 items)	X			
Clinical Indices (e.g. BMI)	X	X	X	X
DES (8 items)	X	X	X	X
EQ-5D-3L (6 items)	X	X	X	X
HADS (14 items)	X	X	X	X
HCUQ (17 items)	X	X	X	X
PAID (20 items)	X	X	X	X
TEI-SF (9 Items)		X		
BFI-10 (10 items)	X			
WSAS (5 items)	X	X	X	X

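### EQ-5D is primary in the abstract and outcome text but secondary in Table 1; if it is primary, the two-outcome sample size no longer supports both study-wide .05 and 80% power

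*Protocol article*

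**What the plan says.** The protocol article gives EQ-5D two different ranks.

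- **Abstract, Methods:** "The primary outcome measures will be generalised self-efficacy (GSE) and health-related quality of life (AQoL-6D and EQ-5D". This names three instruments.
- **Outcome measurements, text:** the sentence on primary measures opens with "Primary measures are changes in: health-related quality of life as assessed by the AQoL-6D [26" and continues with "score and EQ-5D [27]; and self-efficacy as measured by the General Self-Efficacy Scale (GSE) [34". EQ-5D again stands among the primaries.
- **Outcome measurements, Table 1:** only AQoL-6D and GSE appear under the primary heading. The row "EQ-5D-3L (6 items" appears under the secondary heading.
- **Participants, power paragraph:** "The calculations assumed two primary outcomes (health-related quality of life and General Self-efficacy Scale (GSE) scores". The other inputs include "four assessment points (baseline, 3-month, 6-month, and 12-month follow-ups", "a study-wide type I error rate (α) of .05" and "a type II error rate (β) of 0.20 (power of 0.80". The paragraph does not say which instrument carries quality of life, or how alpha is divided.

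Research aims and the economic paragraph of Statistical analyses use both AQoL-6D and EQ-5D as utility measures.

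**The concern.** AQoL-6D and EQ-5D are different instruments and can give different answers. As the article stands, a favourable EQ-5D result could be reported as primary by citing the abstract, and an unfavourable one as secondary by citing Table 1. Fixing the primary outcome in advance is meant to prevent that choice. It matters more here because the outcomes at issue are self-reported and the article says that neither participants nor investigators can be masked.

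The rank also affects the error budget. The trial is sized for two primary outcomes under one study-wide alpha of .05. A third confirmatory test must be paid for with a higher overall error rate or a stricter threshold per test.

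**Working it through.** **Inputs from the power paragraph (Participants):** d = 0.50, study-wide alpha .05, two-sided tests, power 0.80, two primary outcomes, four assessment points, correlation 0.81, 66 evaluable per group, 20% attrition, 166 recruited.

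**Assumptions, not stated in the article:** alpha is shared equally (.05/2 = .025 each), and the variance is that of a mean of four equally correlated assessments. Both are inferred because together they return the stated figure. The article gives no correlations between outcomes, so those below are assumed.

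**1. Reproducing the stated size**

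- Variance factor: f = (1 + 3 × 0.81)/4 = 0.8575.
- n per group = 2 × (2.241 + 0.842)² / 0.50² × 0.8575 = 65.2, rounded up to **66**.
- Attrition: 66/0.80 = 82.5, rounded up to **83 per group, 166 in total**.
- Power at 66: Φ(0.5/√(2 × 0.8575/66) − 2.241) = **0.805**.

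Both stated sizes are matched exactly. A mean of the three follow-ups at .025 gives 67, so the match does not prove the formula. The same four-point mean at an undivided .05 gives 54, which does not match.

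**2. EQ-5D secondary (Table 1)**

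Two tests at .025 give a study-wide error of at most .05 (1 − 0.975² = .049 if independent). Size and power are as in step 1, so nothing changes.

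**3. EQ-5D primary, each of three tests at .025**

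- Upper bound: 3 × .025 = **.075**.
- If independent: 1 − 0.975³ = **.073**.
- By simulation: about **.056 to .070**, for assumed AQoL-6D/EQ-5D correlations of 0.9 to 0.5 and correlations with GSE of 0 to 0.5.

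Power per outcome stays at 0.805.

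**4. EQ-5D primary, .05 split three ways (.0167 each)**

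- n per group = 2 × (2.394 + 0.842)² / 0.50² × 0.8575 = 71.8, rounded up to **72**. With attrition, 72/0.80 = 90 per group, 180 in total.
- Power at 66: Φ(0.5/√(2 × 0.8575/66) − 2.394) = **0.76**.

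| Status of EQ-5D | Alpha per test | Study-wide error | Power at 66 (sizing formula) | Evaluable per group needed |
|---|---|---|---|---|
| Secondary | .025 | at most .05 | 0.805 | 66 |
| Primary, alpha not re-split | .025 | at most .075 | 0.805 | 66 |
| Primary, alpha re-split | .0167 | at most .05 | 0.76 | 72 |

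**The case against.** The strongest reply is that Table 1 and the power paragraph fit together: two primaries, AQoL-6D and GSE, with 66 per group reproduced exactly. On that reading only the abstract and one sentence need editing. This stands. A reader might infer from the contradiction that the stated alpha and power fail outright, and the article does not support that. Under Table 1 both hold. With EQ-5D as a primary, only one of them need fail, depending on whether alpha is divided again.

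A reader might also take the 0.76 to mean that the trial is underpowered. That does not follow. Statistical analyses plans an MMRM at 3, 6 and 12 months with baseline as a covariate, whereas the figure comes from a formula that averages baseline in with the follow-ups. If 0.81 is instead applied as the baseline correlation at a single follow-up, the variance factor is 1 − 0.81² = 0.3439. Power at 66 per group and .0167 is then Φ(0.5/√(2 × 0.3439/66) − 2.394), about 0.99. The 0.76 shows only that the apparent sizing formula would ask for more participants.

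Two further points stand. If AQoL-6D and EQ-5D are strongly correlated, the error inflation lies near the lower end of its range. Detailed multiplicity rules may be in an analysis plan that is not shown, so their absence here is not a finding. Neither point removes the contradiction, because a fuller document could agree with only one of the two ranks that the article gives EQ-5D.

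**Conclusion.** Wrong as written: an internal contradiction about which quality-of-life result is confirmatory. It needs correcting before analysis, because a choice made later could follow the data.

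The need rests on the unclear primary outcome, not on a demonstrated failure of alpha or power. The consequence for the error budget is conditional and moderate. If EQ-5D is secondary, there is none. If it is primary, either the study-wide error rises above .05 to at most .075, or the sizing formula asks for 6 more evaluable participants per group (72 against 66). These figures depend on the inferred .025 split and four-assessment mean, and the .056 to .070 range also depends on assumed correlations between outcomes.

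**What to change.** Give EQ-5D one status in the abstract, the outcome text, Table 1 and the power paragraph.

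The least costly choice follows Table 1 and the power paragraph:

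- Name the AQoL-6D global utility score and GSE as the two primary outcomes. The article describes AQoL-6D as six dimension scores plus a global one, so the score should be named.
- State how the study-wide .05 is shared over the two, for example .025 each or Holm.
- List EQ-5D-3L as secondary, contributing to QALYs alongside AQoL-6D.
- Correct the abstract and the outcome sentence, and check that the registry entry agrees. It was not available for this review.

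If three primaries are intended, state the multiplicity rule and restate the alpha and power figures.

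The first option costs a wording amendment, with no change to data collection or to the 166 participants. Its downside is that the sponsor gives up claiming primary success on EQ-5D.

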**Discussion:**

We envisage that the Optimal Health Program’s emphasis on self-efficacy and self-management will provide participants with the skills and knowledge to achieve increased empowerment and independence in aspects of health, which in turn, will help participants deal more effectively with the physical and psychosocial complexities of diabetes.

**Trial registration:**

ACTRN12614001085662. Registered on 10 October 2014.

## Background

There are an estimated 382 million people globally with diabetes mellitus (DM) − a prevalence of 8.3 % [1]. Far more people are estimated to have blood glucose levels in the prediabetes range, with an increased risk for type 2 diabetes, placing a significant proportion of the world’s population at risk of developing devastating diabetes complications [2]. Diabetes is usually incurable and requires daily and complex self-management; and attention to psychological issues is pivotal to achieving optimum health outcomes [3]. Psychological disorders, including depression, anxiety, maladjustment and eating disorders are highly prevalent in children and adults with DM and are associated with poor prognosis [4–8]. Recognition of such concerns has prompted the incorporation of psychological aspects of DM in national standards of care [4, 9].

At the centre of diabetes care is maintaining optimal glucose target ranges. This is highly reliant on a person’s successful negotiation of healthcare systems and coordination with clinicians [10]. Even when blood glucose levels are within targets, hypoglycaemia can contribute to fear, anxiety and has been associated with decreased quality of life [11]. Emerging evidence suggests that severe nocturnal hypoglycaemia is linked to ‘dead in bed’ syndrome, responsible for approximately 6 % of deaths in people with diabetes aged less than 40 years of age [12]. Understandably, fear of hypoglycaemia is common and difficult to distinguish from anxiety given the shared symptoms e.g., pounding heart, sweating. Improving awareness of anxiety as distinct from hypoglycaemia may encourage persons with diabetes to respond more rapidly, potentially averting a severe episode of illness [11].

Similarly, depression and diabetes have an overlapping relationship, lending further support for holistic programs that facilitate exploration of physical and emotional domains of health. On a biological level, one hypothesis is that depression (which often co-occurs with anxiety) is associated with glucose metabolism via activation of the hypothalamic–pituitary–adrenal cortical (HPA) axis, though the specificity of this link to depression versus other psychiatric conditions is unclear [13]. People who are depressed may also have low motivation and energy, adversely impacting diabetes self-management tasks. Vice versa, if diabetes self-care is challenged, or a person becomes increasingly hopeless about developing complications, a depression presentation can arise. Depression can also present in the context of direct mood effects of chronic hyperglycaemia (high blood sugar).

This evidence highlights the bi-directional relationships between diabetes and mental health, present across the spectrum from mild to more severe clinical presentations. Through supporting emotional wellbeing, it is clear to see how improvements in diabetes can follow, and vice versa, with good support. This randomised controlled trial (RCT) of Mental Health in Diabetes Services Optimal Health Program (MINDS OHP) will adopt a person-centred approach combining collaborative therapy and care coordination to support and improve the psychosocial health of people living with DM.

### Diabetes psychosocial interventions

Diabetes is a challenging condition due to the complex interactions between physiological, psychological and environmental factors and its evolving nature [14, 15]. Recently, interventions and guidelines have minimised advocacy of a hierarchical clinician/patient relationship in favour of a collaborative approach to be delivered by a multidisciplinary team that tailors interventions to each individual’s situation [4, 9, 16]. As such, shared decision making, pragmatic problem solving and promotion of behaviour change strategies are integral to achieving sustainable self-management of DM [4, 5]. Growing evidence has been presented for the use of psychosocial interventions in people with DM, yet questions regarding their efficacy remain [17].

A recent RCT that assessed the effectiveness of cognitive behaviour therapy (CBT) to improve glycaemic control and psychosocial wellbeing in adolescents with type 1 DM (n = 147), demonstrated little improvement in glycaemia [18], but improvements in psychosocial wellbeing (self-efficacy and quality of life) were shown at 3- and 12-month follow-up. Challenges were also noted in the integration of psychosocial services into clinical care, including cost-effectiveness issues, intervention participation, acceptance and attrition [18].

A systematic review and meta-analysis of psychotherapy, antidepressant medication and collaborative care for comorbid DM and depression (14 RCTs; n = 1724) showed that pharmacotherapy and collaborative care reduced depressive symptoms; however, with the exception of sertraline, there was no effect on glycaemic control [5]. The authors concluded that collaborative care containing psychological and pharmacological components is of considerable clinical relevance, although a strong emphasis on DM management and further research into type 1 DM specifically is warranted [5].

A Cochrane review of psychological and pharmacological interventions for depression in DM (eight RCTs; n = 1122) found a moderate and clinically significant effect on depression [6]. Also noted was sparse and inconclusive evidence in relation to the influence of psychological intervention on blood glucose levels, largely due to substantial risk of bias and heterogeneity of populations and interventions [6]. Similar findings regarding CBT and glycaemic control in DM were also reported in another systematic review and meta-analysis (eight studies; n = 1547), which revealed a non-significant trend towards improved blood sugar levels (BSLs) [19].

Recent evidence has established that effective disease management of DM requires strengthening of psychosocial skills, ideally within a collaborative therapy framework integrated with usual medical care [4, 5, 16]. A number of challenges have also been noted including: cost-effectiveness, participation and attrition rates, and delivery that complements and coexists with usual DM health care [6, 17, 18]. As DM has reached epidemic proportions [1]; new and innovative ways of managing it are essential. The MINDS Optimal Health Program (MINDS OHP) adopts a collaborative therapy approach that offers structured yet individualised multidisciplinary support and education to enhance self-efficacy and the psychosocial wellbeing of people with type 1 and type 2 DM. The program recognises that though there are shared psychosocial impacts, type 1 and type 2 diabetes have separate aetiologies and disease processes which will be taken into account in delivering and evaluating the MINDS OHP.

### Translating Research, Integrated Public Health Outcomes and Delivery (TRIPOD)

This RCT is part of a larger research program, TRIPOD, which will evaluate our OHP across three chronic conditions − DM, stroke and chronic kidney disease − inclusive of cost-effectiveness analyses. Based on a collaborative therapy framework [20], the OHP was originally developed to support people with mental illness [21, 22]. An earlier trial of OHP in an Australian adult mental health service demonstrated significant improvements in health and social functioning, a reduction in hospital admissions and net cost savings of AU$6,000 per patient annually [22]. A key aspect of collaborative therapy is recognising that ‘recovery’ and models of chronic health care are not dichotomous [22]. With the intention of enhancing self-efficacy, self-management, care coordination and quality of life, the OHP has been adapted within the broader context of chronic disease. Thus, in the current series of trials our OHP is used to implement this therapeutic framework to enable clinicians and consumers to work systematically towards the achievement of optimal mental health outcomes within mainstream services. The self-management foundations of the OHP are particularly relevant for adults with DM who face the daily challenge of managing often simultaneous aspects of their disease such as diet, exercise, insulin delivery, carbohydrate counting, and blood glucose monitoring, as well as coping with the emotional impact of their condition and care regimen. This protocol describes an RCT (MINDS OHP) that has been designed to evaluate the OHP for people living with DM.

### Pilot study: clarifying the experience of insulin pump users

Adaptation of the OHP for people with DM was informed by anecdotal evidence, a review of the associated literature, and pilot data. Preliminary work to inform the content and structure of the MINDS manual compromised focus groups of adults with T1DM (two focus groups; n = 3, n = 2, and one individual participant interview) that specifically explored the adaptability of the OHP to DM. The six domains of health from the ‘Optimal Health Wheel’ used in the original OHP were used to guide the direction of discussions (Fig. 1, inner circle). The Framework Method was deemed appropriate to analyse the qualitative content of the focus group data as it provides a systematic model for identifying themes via managing and mapping the data [23]; a specific area of interest was how people dealt with insulin pump therapy [24, 25].

**Fig. 1 Fig1:**
[figure not shown]
Optimal Health Program (OHP) Optimal Health Wheel (*inner circle*) and diabetes mellitus (DM) pilot study findings (*outer circle*)

Findings from the focus groups highlighted the importance of self-perception in living and coping with DM. The emotional domain dominated focus group discussions; key themes identified were: a sense of helplessness in gaining control over DM, flexibility of the pump in daily lifestyle; pump malfunction; low self-esteem and self-efficacy regarding adequate management of blood glucose levels; and ongoing concerns about similar ‘out of their control’ experiences in the future. These findings highlight the need for psychosocial supports in the management of DM, especially in regard to self-reflection, problem solving and stress management. Self-efficacy is at the centre of OHP and it is therefore well-placed to support those living with DM. A summary of the findings/themes identified by people with DM associated with each of the Optimal Health Wheel domains are presented in Fig. 1 (see Fig. 1, outer circle).

